# Community-based lifestyle intervention for diabetes (Co-LID study) management in rural Nepal: study protocol for a clustered randomized controlled trial

**DOI:** 10.1186/s13063-023-07451-5

**Published:** 2023-07-05

**Keywords:** Type 2 diabetes mellitus, Lifestyle intervention, Health behaviour, Community-based, Cluster randomized controlled trial

## Abstract

**Background:**

Type 2 diabetes mellitus (T2DM) has increased globally; with a disproportionate burden in South and Southeast Asian countries, including Nepal. There is an urgent need for clinically and cost-effective culturally adapted T2DM management programs. In this study, we aim to assess the effectiveness of community based culturally appropriate lifestyle intervention in improving the management and care of people with T2DM.

**Methods:**

We will conduct a cluster randomized control trial to evaluate the effectiveness of community based culturally appropriate lifestyle intervention in improving T2DM outcomes. The trial will be conducted in 30 randomly selected healthcare facilities from two purposively selected districts (Kavrepalanchowk and Nuwakot districts) of Bagmati province, Nepal. The selected healthcare facilities are being randomized into 15 interventions (*n* = 15) and usual care (*n* = 15) groups. Those in the intervention will receive group-based 12 an hour-long fortnightly session delivered over 6 months period. The intervention package includes 12 planned modules related to diabetes care, ongoing support, supervision and monitoring, follow-up from the trained community health workers, and educational materials on diabetes self-management. The participants in the usual care groups will receive pictorial brochure on diabetes management and they will continue receiving the usual care available from the local health facilities. The primary outcome is HbA1c level, and the secondary outcomes include quality of life, health care utilization, and practice of self-care behaviour, depression, oral health quality of life, and economic assessment of the intervention. Two points measurements will be collected by the trained research assistants at baseline and at the end of the intervention.

**Discussion:**

This study will provide tested approaches for culturally adapting T2DM interventions in the Nepalese context. The findings will also have practice and policy implications for T2DM prevention and management in Nepal.

**Trial registration:**

Australia and New Zealand Clinical Trial Registry (ACTRN12621000531819). Registered on May 6, 2021.

**Supplementary Information:**

The online version contains supplementary material available at 10.1186/s13063-023-07451-5.

## Introduction

Globally, type 2 diabetes mellitus (T2DM) accounts for 90–95% of all cases of diabetes and contributes to around 3% of total disability-adjusted life years (DALYs) [1–3]. The International Diabetes Federation (IDF) reported that 537 million adults were living with diabetes in 2021 and projected to reach 784 million by 2045 [4]; with global expenses around US$ 966 billion in 2021 and are projected to reach US$ 1054 billion by 2045 [4]. The IDF’s estimates indicate that more than 75% of people with diabetes live in low and middle-income countries (LMICs) [4]. Recent data suggest that the larger proportion of people with T2DM resides in South and Southeast Asian countries [4, 5]. In 2021, around 90 million adults (aged 20–79 years) were living with diabetes in the Southeast Asia region and 51.2% remained undiagnosed [4, 6]. T2DM imposes significant economic burden on patients, their families, health systems, and national economies, both directly due to treatment costs or indirectly because of loss of productivity [7].

Over the years, Nepal has been experiencing an increased burden of noncommunicable diseases (NCDs) including T2DM [8]. The prevalence of T2DM among adults in Nepal is estimated to be 8.5%, and a further 5.7% had raised blood glucose levels. A 2020 systematic review reported a pooled diabetes prevalence of 8.5% in Nepal [9]. Furthermore, a WHO Stepwise Surveillance (STEPS) survey reported 5.8% of adult Nepalese population in 2019 had raised blood glucose [10]. T2DM has represented a significant financial burden for Nepal, resulting in US$ 115.8 million in total diabetes-related health expenditure in 2021, and projected to reach US$ 190.5 million by 2045 [4]. Evidence also shows that the prevalence of T2DM risk factors is very high. For example, in 2019, the WHO STEP survey reported that around 24% of Nepalese were overweight and had raised blood pressure (BP), 17% had smoking behaviour, 11% had high cholesterol levels, 8% had insufficient levels of physical activity, 7% people consumed alcohol (highest 12% in the male), and 97% participants did not consume sufficient fruits and vegetables [10]. This suggests that the number of T2DM cases will continue to grow in the coming years.

Inadequate access to and use of healthcare services and high out-of-pocket expenses for management and care can increase the likelihood of T2DM complications, which in turns become a significant burden for the individuals and healthcare system. Therefore, there is an urgent need for developing clinically and cost-effective culturally appropriate health behaviour interventions to improve T2DM outcomes. In this study, we aim to assess the effectiveness of community based culturally appropriate lifestyle intervention in improving the management and care of people with T2DM.

## Methods

### Trial design

This study follows prospective, single-blinded end-point assessment of a 2-arm randomized controlled trial (RCT) with blinding of the statistician in order to perform cluster randomization. The intervention time is 6 months with assessments of outcomes at baseline and at the end of the intervention. This protocol was designed in accordance with the Standard Protocol Items: Recommendations for Interventional Trials (SPIRIT) Statement (Cite) (Additional file 1) [11].

### Study setting

This community-based lifestyle intervention for diabetes (Co-LID study) management is being implemented in two selected districts (Kavrepalanchowk and Nuwakot districts) of Bagmati province, Nepal (Fig. 1). The total population of Kavrepalanchowk district is 366,879 [12], and there are altogether 172 health facilities (132 public and 40 private) within the district [13]. Similarly, Nuwakot district comprises 262,981 people [12] with 97 healthcare facilities (83 public and 14 private) within the district [13]. In this study, the health centres such as health posts, primary health care centres, urban health centres, community health units, and the outreach centres of Dhulikhel hospital in Kavrepalanchowk and Nuwakot district are being considered as the clusters. The baseline and endline data will be collected from the participants from all clusters (both intervention and usual care arms).

**Fig. 1 Fig1:**
[figure not shown]
Map of Kavrepalanchowk and Nuwakot districts with selected study clusters/health facilities

### Study population

The target participants of this interventional study are those clinically diagnosed with T2DM and aged 30–70 years who are capable for coping with active lifestyle management. Those who have clinically diagnosed type 1 diabetes mellitus, currently pregnant, below the age of 30 years, and with mental illness were excluded in this study. The interventional group will receive the allocated interventional packages in the local healthcare facility as scheduled.

### Clusters

Unit of cluster for this study are healthcare facilities within the districts with at least 12 people in each cluster who are clinically diagnosed with T2DM. In total, 30 clusters from both districts are being selected adopting the stratified random sampling. The selected clusters will be randomly allocated as intervention and usual care groups in 1:1 ratio. To avoid the inter-cluster contamination, the nearby/neighbouring clusters are allocated as usual care and intervention groups. The interventions will be evaluated with two cross-sectional surveys, i.e. at baseline and in endline after the 6 months of interventions (Fig. 2).

**Fig. 2 Fig2:**
[figure not shown]
CONSORT diagram of the community-based T2DM intervention in Nepal

### Randomization

The participants meeting the inclusion criteria and able to provide the consent for their participation in the study will be randomly allocated to intervention and usual care arms. A total of 30 clusters that met the inclusion criteria (i.e. 20 health centres from Kavrepalanchowk and 10 from Nuwakot districts) are being randomly allocated into 15 interventional clusters and 15 usual care clusters by the statistician not involved in this study.

### Sampling

Healthcare facilities, primarily the ones run by the public sector, have been considered as study sites. There are a total of 269 public and private healthcare facilities (i.e. 172 in Kavrepalanchowk and 97 in Nuwakot) in these selected districts of Nepal [13]. Stratified random sampling technique was adopted to enrol the 30 study sites (15 each from Kavrepalanchowk and Nuwakot district) if the health centres meet the criteria of 12 type 2 diabetes participants that could be enrolled in our study. With this, we will use Health Management and Information Systems (HMIS) registries of selected healthcare facilities to identify the people clinically diagnosed with T2DM. Given the record keeping of NCDs including diabetes in HMIS registries is not mandatory in public health care facilities, we also organized the diabetes screening camps in those places to identify the people with T2DM. All patients clinically diagnosed with T2DM and those diagnosed during the screening camps were enrolled in the study. Those diagnosed with T2DM in the screening camps were sent to nearest health facility and pathology for confirmatory test before they were enrolled in the study. At least 12 people clinically diagnosed with T2DM were required in each cluster. The clusters were then randomly allocated into intervention or usual care arms (Fig. 2).

### Sample size

The aim of this study is to assess the effectiveness of intervention in terms of reduction of mean HbA1c levels from 7.5% at baseline to 7.0% at 6 months follow-up among the intervention participants compared with estimated no or minimal changes in participants of usual care arm (HbA1c levels 7.5%), with at least 80% power and 95% confidence interval (CI) and assuming an intra-class correlation coefficient (ICC) of 0.050 and estimated HbA1c mean standard deviation (SD) of 1.3, as reported in studies that used diabetes self- management programs in the past [14]. The cluster RCTs implemented in similar settings of the Asian subcontinent in the past have used ICC of 0.02 [15] to 0.05 [16]. Allowing for cluster randomization with 15 clusters each arm, a minimum of 12 individuals would be required per cluster, equating to a total sample size of 180 per arm at 6 months follow-up. With the adjustment of possible maximum 15% attrition rate at 6-month follow-up, we required 211 participants in each arm at the baseline.

#### Recruitment of community health workers (CHWs)

Community health workers are the peripheral frontline health workers of the government health facilities (Primary Health Centre, Health Post, Urban Health Centre) and outreach centres of Dhulikhel Hospital. Any two CHWs (Auxiliary Nurse Mid-wife, Auxiliary Health Worker or Health Assistant) from each of selected health facilities willing to participate in this intervention are enrolled and the consent from their respective health facility in-charge was sought to get them involved in the study. The selected CHWs are trained in terms of health behaviour, patient empowerment, social and emotional support, and overall T2DM self-management by diabetologist, nurse practitioner, physician and oral health specialist, etc.

#### Recruitment of peer supporters

Peer supporters are those individuals who have experiential knowledge of a specific behaviour or stressor and similar characteristics as the target population [17]. Those meeting the eligibility criteria for this study and expressed interest to self-manage lifestyle themselves and help others are identified and invited to act as peer supporters for the study. Those who accept to act as peer supporter are selected and trained to closely work with the trained community health workers (from the respective study site) and provide necessary support to organize the group-based sessions of the intervention such as invitation to sessions, talking to participants, social and emotional support, and encourage to adhere to healthy lifestyles by setting an example. Two peer supporters are recruited from each of the clusters in an interventional arm.

### Interventions

The community-based intervention comprises of combination of intensive training sessions on diabetes self-management programs that include dietary measures, stress management/problem solving, ways to stay away from triggers to drink alcohol and smoke, diabetes medications, diabetes literacy, monitoring blood sugar level, physical activity, health care utilization, oral health, foot care, quality of life, and social and emotional support. These are the group-based (group consists of all participants of a particular cluster of an intervention arm) fortnightly 1-h long counselling sessions to be conducted by trained CHWs. We have altogether 12 modules that are to be conducted fortnightly for 6 months. During the counselling sessions, we will fill the gaps in the participant’s knowledge and empower participants to take the decision to change their lifestyle to prevent complications associated with diabetes. We will have empathetic listening if participants want to share their queries and experiences. In addition, a pictorial book on diabetes management and prevention of complication in Nepali language with the same content as delivered in the group-based counselling sessions will be provided to the study participants. Apart from this, an automated phone call and text messages will be delivered to the participants to remind them of the upcoming fortnightly training sessions. See Additional file 2 for summary intervention modules (Additional file 2).

Moreover, a trained CHW will conduct a fortnightly telephone call session for the first 3 months and then the monthly calls for the rest of the months to ensure adoption and maintenance of healthy self-care behaviours (i.e. healthy eating, physical activities, blood sugar monitoring, taking medicine, foot care, acute and chronic complications awareness, healthy coping, problem solving and reduction of complications) among the study participants [18]. Additionally, online messages (pictorial and audio visual) on lifestyle intervention using mobile phones and smartphones will be delivered to the interventional group over a period of 6 months.

### Usual care

Usual care group will receive standard diabetes management and care provided in accordance with usual care in the selected location. In addition, a pictorial book on diabetes prevention education in Nepali language will be provided in order not to deprive them from awareness raising.

### Outcome measures

The primary outcome measure of this study are glycated haemoglobin levels as defined by the WHO [19]. Secondary outcome measures include quality of life, health care utilization, and practice of self-care behaviour and economic assessment of health behaviour interventions. The primary and secondary outcome measures are briefly presented in Table 1.

**Table 1 Tab1:** Summary of outcome variables

**Outcomes**		**Measurement tool**
***Primary outcome***		
Glycated haemoglobin (HbA1c) levels		Blood
***Secondary outcomes***		
Quality of life	General	SF-8 [20], EQ-5D [21]
	Diabetes and oral health	Oral Health Impact Profile (OHIP-14) [22]
	Diabetes distress	Perceived Stress Scale (PSS) [23]
	Depression	PHQ-9 [24]
	Blood pressure	NDHS STEPS survey [14]
	Body mass index (BMI)	NDHS STEPS survey [14]
Program effectiveness (process evaluation)		Training for community health workers using Training of Trainers (TOT) modality for local capacity building, training for peer supporters focusing on facilitation and communication skills, monthly peer support meeting, follow-up
Healthcare utilization		Access to healthcare services Visit to health facility in last 6 months Specialist visits in last 6 months
Practice of self-care behaviours		24-h dietary recall and fruits and vegetable intake in a week adapted from SDSCA [15], NDHS STEPS survey for physical activity, MMAS-8 [16] for medication intake
Economic evaluation	Cost-estimation	No. of visits past 6 months to diabetes clinician/endocrinologist No. of visits past 6 months to other clinicians No. of visits past 6 months for emergency/acute care No. of overnight stays past 6 months in hospital (related to your diabetes)
	Cost-effectiveness analysis	Cost of healthcare resource use and EQ-5D
	Long-term economic impact analysis	Markov modelling

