#### Economic evaluation

Cost, cost-effectiveness and returns of investment analysis will be conducted in the healthcare and societal perspective. Cost of the healthcare resource use will be collected from the study participants and cost of implementing the interventions will be collected prospectively from the project accounts by using the standardize Excel sheet design especially for this project. Incremental cost-effectiveness ratios (ICERs) per quality-of-life year (QALY) gained and returned on investment (ROI) ratio will be calculated, and the robustness of the results will be assessed through sensitivity analysis. In addition, Markov model will be applied to forecast the long-term economic impact of the health behaviour intervention.

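### Health-facility visits in the last 6 months are compared between arms, yet the intervention is itself delivered at that facility and no rule excludes its sessions

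*Protocol article*

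**What the plan says.** **Outcome.** Table 1 lists "Visit to health facility in last 6 months" under healthcare utilisation, a secondary outcome. The Intention-to-treat analysis section names utilisation among the behaviours whose proportions are compared between arms at the end of the 6 months, using mixed models with a random cluster effect.

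**Delivery.** Under Study population: "The interventional group will receive the allocated interventional packages in the local healthcare facility as scheduled". Under Interventions: "We have altogether 12 modules that are to be conducted fortnightly for 6 months", as "fortnightly 1-h long counselling sessions to be conducted by trained CHWs". Under Recruitment of community health workers: "Community health workers are the peripheral frontline health workers of the government health facilities", with outreach centres of the named hospital added to the list.

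**Timing.** Data collection places the endline interview 6 months after enrolment and says that the baseline process is repeated then.

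**Costs.** The cost-estimation row of Table 1 has four items: visits to a diabetes clinician, "No. of visits past 6 months to other clinicians", emergency visits and hospital nights. The Economic evaluation section says that the analyses "will be conducted in the healthcare and societal perspective". Participants supply the cost of the healthcare they use, and the "cost of implementing the interventions will be collected prospectively from the project accounts".

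**Registry.** Process evaluation keeps a register of educational sessions. It is not linked to the visit counts or the costing.

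**The concern.** A visit count is meant to show whether people sought care differently. Here one arm is invited to the facility every fortnight as the intervention itself, and facility staff run the sessions. A participant who is asked at endline about facility visits over the past 6 months can reasonably count them. At baseline the item is harmless, because no sessions have taken place; at endline it depends on arm.

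The analysis section groups utilisation with behaviours taken as adherence to lifestyle change, so the artefact would read as benefit. The random cluster effect and covariate adjustment cannot remove it, because session attendance occurs in one arm only.

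Two cost questions follow. If sessions are also reported as visits to other clinicians, they could enter the costs a second time, since delivery is already costed from project accounts. Separately, the stated societal perspective is wider than the cost inputs that the article lists.

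**Working it through.** **1. Inputs from the document.** 12 sessions of 1 hour, fortnightly (Interventions); delivery at the local facility (Study population); recall of 6 months (Table 1); endline 6 months after enrolment (Data collection); 15 clusters of 12 per arm and 15% attrition (Sample size).

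**2. The plan's own figures.** The document gives no expected visit rate, so there is no utilisation figure to reproduce. The denominators do reproduce: 15 × 12 = 180 per arm at follow-up, and 180 / 0.85 = 211.8 against the stated 211 at baseline. The point does not depend on them.

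**3. Does the recall window cover the sessions?** Twelve fortnightly sessions occupy 12 × 2 = 24 weeks, and 6 months is about 26 weeks. If sessions start soon after enrolment, essentially all of them fall inside the window.

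**4. Effect on a visit count.** Added attendances per intervention participant = 12 × attendance; in usual care, 0. Attendance is assumed:

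| Attendance | Added per participant | Added in the arm (n = 180) |
|---|---|---|
| 25% | 3 | 540 |
| 50% | 6 | 1,080 |
| 75% | 9 | 1,620 |
| 100% | 12 | 2,160 |

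At 75% attendance, with every attended session reported as a visit, an assumed usual-care mean of 1, 2, 3 or 6 visits becomes 10, 11, 12 or 15 in the intervention arm. These are ratios of 10, 5.5, 4 and 2.5, with no change in care-seeking.

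**5. Effect on an any-visit proportion.** Let p be the proportion who would have had a visit anyway, s the proportion who attend at least one session, and r the share of those attenders who report sessions as visits. Taking these as independent, the artificial difference is (1 − p) × s × r.
- With only 25% attendance at each session, independent across sessions, s = 1 − 0.75^12 = 0.968.
- With r = 1: p = 0.5 gives 0.5 × 0.968 = 0.48, and p = 0.8 gives 0.2 × 0.968 = 0.19.
- With r = 0.25: 0.48 × 0.25 = 0.12 and 0.19 × 0.25 = 0.05.
- With r = 0 there is no artefact.

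The values of p, r and attendance are all assumed, so this shows a range and does not estimate the bias.

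**6. The cost side.** The facility-visit item is under utilisation and is not among the four cost-estimation items. A session reaches the costs a second time only if a participant reports it under another heading, most plausibly visits to other clinicians.

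**7. The societal perspective.** The four items are health-service contacts, and the cost-effectiveness row names healthcare resource cost and EQ-5D. The Introduction counts lost productivity as part of the burden of diabetes, but no time, travel or productivity input is listed. Session time alone is up to 12 × 1 h = 12 h per participant, or 12 × 180 = 2,160 h per arm. With an assumed round trip of 0.5 to 3 h it is 12 × 1.5 = 18 h to 12 × 4 = 48 h per participant.

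**The case against.** The strongest reply is that this is a condensed article. Table 1 is a summary, and the questionnaire and costing sheet are not shown. An interviewer instruction to ignore programme sessions could exist, and a table label is not a counting rule. That stands as a limit: the document does not say that sessions count as visits. It does not answer the point, however, because the outcome as published overlaps with the intervention, and nothing in the text separates the two.

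Four stronger readings are tempting, and the document does not support them.
- **Facility visits are a listed cost input.** They are not; the cost-estimation row has other items.
- **Sessions are certainly costed twice.** This requires participants to report a counselling group led by health workers as a visit to another clinician. That is possible, but it is not stated.
- **Participants' out-of-pocket costs or time are not collected.** The Economic evaluation section does collect the cost of healthcare use from participants, which may include payments for care. Time and travel are not listed, which is different from not being collected.
- **The cost-effectiveness ratio is biased in a known direction.** Double counting would work against the intervention and omitted attendance time would favour it. Omitted productivity gains, if there are any, would work against it. The net direction is unknown.

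Timing is also a fair objection. Trial status has data collection in progress and the endline around mid-2023, so rewording may come too late for some or all interviews.

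**Conclusion.** The point holds for the utilisation outcome. As published, the item can differ between arms because of where the intervention is delivered: by up to 12 attendances per intervention participant against 0 in usual care, if sessions are attended and reported as visits. For an any-visit proportion, the size depends on usual-care visit rates, attendance and reporting, which the document does not give. The percentages above illustrate it under assumptions and should not be cited as the expected bias.

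On costs the conclusion is narrower. Double costing of sessions is a conditional risk. The claimed societal perspective is not matched by the inputs listed. Neither point shows that a cost-effectiveness result would be wrong in a particular direction.

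The primary outcome, HbA1c, and the sample size are unaffected.

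**What to change.** 1. Define the endline utilisation outcome as facility visits other than attendance at Co-LID group sessions, and apply the same exclusion to the cost item on visits to other clinicians.
2. Cost the sessions once, from project accounts.
3. If endline interviews are already done, use the session registry, provided that it records individual attendance. Remove session visits from the counts, or report the result with and without attended sessions subtracted. If the item was recorded only as yes or no, subtraction is not possible and only a sensitivity analysis remains.
4. Either name the time, travel and productivity inputs that support the societal perspective, or state the healthcare perspective only.

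**Cost.** A short instruction on two endline items and a sentence in the analysis description. The endline wording would differ slightly from baseline, which matters little because no sessions had taken place by then. Using the registry requires linking attendance to participants. Item 4 is a clarification if the inputs already exist; otherwise it means a few added questions or a narrower claim.
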